## Abstract

**Background:**

Vascular disease, manifesting as myocardial infarction and stroke, is a major cause of morbidity and mortality, especially in low- and middle-income countries. Current estimates are that only one in six patients have good adherence to medications and very few have sufficient health literacy. Our aim is to explore the effectiveness and acceptability of Prescription Interactive Voice Response (IVR) Talking Prescriptions (Talking Rx) and SMS reminders in increasing medication adherence and health literacy in Pakistani patients with vascular disease.

**Methods:**

This is a randomized, controlled, single center trial. Adult participants, with access to a cell phone and a history of vascular disease, taking multiple risk-modifying medications (inclusive of anti-platelets and statins) will be selected from cerebrovascular and cardiovascular clinics. They will be randomized in a 1:1 ratio via a block design to the intervention or the control arm with both groups having access to a helpline number to address their queries in addition to standard of care as per institutional guidelines. Participants in the intervention group will also have access to Interactive Voice Response (IVR) technology tailored to their respective prescriptions in the native language (Urdu) and will have the ability to hear information about their medication dosage, correct use, side effects, mechanism of action and how and why they should use their medication, as many times as they like. Participants in the intervention arm will also receive scheduled SMS messages reminding them to take their medications. The primary outcome measure will be the comparison of the difference in adherence to anti-platelet and statin medication between baseline and at 3-month follow-up in each group measured by the Morisky Medication Adherence Scale. To ascertain the impact of our intervention on health literacy, we will also compare a local content-validated and modified version of Test of Health Literacy in Adults (TOFHLA) between the intervention and the control arm.

We estimate that a sample size of 86 participants in each arm will be able to detect a difference of 1 point on the MMAS with a power of 90 % and significance level of 5 %. Accounting for an attrition rate of 15 %, we plan to enroll 100 participants in each arm (total study population = 200). We hypothesize that a linguistically tailored health IT intervention based on IVR and SMS will be associated with an improvement in adherence (to anti-platelet and lipid-lowering medications) and an improvement in health literacy in Pakistani patients with vascular disease.

**Discussion:**

This innovative study will provide early data for the feasibility of the use of IT based prescriptions in an lower middle incorme country setting with limited numeracy and literacy skills.

**Trial registration:**

Clinical Trials.gov: NCT02354040 − 2 February 2015

**Electronic supplementary material:**

The online version of this article (doi:10.1186/s13063-016-1244-1) contains supplementary material, which is available to authorized users.

## Background

Vascular risk, manifesting as myocardial infarction (MI) and stroke, contributes to about 3.87 million premature deaths in the 30–69 year-old age group in Pakistan [1]. In one of the largest case-control studies of 15,152 cases of first MI and 14,820 controls, it was shown that South Asian participants were relatively young at the time of their first MI (mean age = 53 years) compared with participants from China or Western Europe (mean age = 63 years) [2]. Nearly 10 % of these heart attacks in South Asian participants occurred in individuals aged 40 or below. Similarly, the reported lifetime prevalence of stroke symptoms is 19 % in urban Pakistan, which amounts to 7 million potential cerebrovascular victims in this densely populated high-risk region [3].

Although most patients admitted with acute coronary syndrome or acute ischemic stroke in South Asian countries receive these evidence-based treatments, their overall continuation in the outpatient phase of care remains low. Patients from Pakistan are uniquely challenged in this respect because the overall literacy rates remain one of the lowest in Pakistan among South Asian countries. In addition, a great majority of Pakistani patients often do not understand or follow health prescriptions (which are still written in English). Additionally, due to an unregulated health industry, patients frequently take multiple opinions and prescriptions from different physicians [1, 4]. This lack of understanding leads to a reduced adherence to these often life-saving medications and increases their risk for drug-drug interactions and serious adverse reactions.

The purpose of this study is to develop and pilot test a tailored health information technology-driven intervention in Pakistani patients with coronary artery disease (CAD) and ischemic strokes receiving care in outpatient setting in the Aga Khan University Hospital (AKUH) in Karachi, Pakistan. We hypothesize that this health IT-driven intervention would address the above-mentioned information gaps and will lead to an increase in medication adherence. Furthermore, we hypothesize that this health IT-driven intervention with improve health literacy in this literacy-challenged, resource-poor population.

## Methods

### Design overview

The *Bolta Parcha* (Talking Prescription; Talking Rx) trial is a randomized, controlled, single center superiority trial with blinded outcome assessment. (Fig. 1 – Study flow chart) Adult participants, with access to a cell phone and a history of vascular disease longer than 1 month of duration, who are taking multiple risk-modifying medications (inclusive of anti-platelets and statins) will be selected from neurology and stroke clinics at the AKUH.

**Fig. 1 Fig1:**
[figure not shown]
Study flow chart. Standardized Consolidated Standards of Reporting Trials (CONSORT) flow for the Talking Prescription (Talking Rx) program

They will be randomized into two parallel groups (intervention group and control group) in a 1:1 ratio via block technique. Both groups will have access to a helpline number to address their queries regarding their illness and medications in addition to receiving the standard of care as per institutional guidelines. In addition, participants in the intervention group will also have access to Interactive Voice Response (IVR)-based informative voice messages tailored to their respective prescriptions. The intervention group will also receive daily tailored text messages regarding dosage and frequency of intake of statins and anti-platelet medications. They would also receive weekly text message reminders to improve medication adherence, lifestyle changes, medication information, risk factors and motivation to improve adherence. These messages are modeled on Social Cognitive Theory and the Health Belief Model and are categorized by Michie’s Taxonomy of Behavioral Change Communication [5, 6].

Patients’ adherence to medications will be assessed using the Morisky Medication Adherence Scale (MMAS) [7]. In a sub-set of patients (20 % of patients in each group), pill count will be performed to assess the correlation between self-reported MMAS and direct pill count. Patient’s health literacy will be measured at baseline and then after 3 months in each group by using Likert’s Scale for Health Intelligence Literacy, Knowledge of Medications, and a modified version of Test of Health Literacy in Adults (TOFHLA) (modified version) [8–10]. The difference in adherence to medication regimen (and health literacy) before and after the intervention will be compared between the two groups to determine the effectiveness of our intervention.

### Study setting

The trial is being conducted in the cardiology and neurology clinics at the AKUH, Karachi, Pakistan. The center is a Joint Commission International Accreditation (JCIA) accredited tertiary care hospital located in Karachi, a large metropolitan city located in the south of Pakistan. The center also has logistic and technical expertise available from dedicated research support staff and an independent Clinical Trials Unit (CTU) and Aga Khan Development Network e-Health Resource Center (AKDN eHRC).

### Participants

Participants attending neurology and cardiology clinics at AKUH are recruited as study participants based on the following criteria:

#### Inclusion criteria

Age older than 18 yearsHistory of stroke(s) or CAD (MI, unstable angina, or coronary intervention performed via percutaneous coronary intervention or coronary artery bypass grafting (CABG)) confirmed using objective modalities at the time of the episode (i.e., neuroimaging, electrocardiogram (ECG), relevant blood tests and physician examination and clinical confirmation in medical records)More than 1 month since last episode of stroke or admission for CAD as described aboveUse of anti-platelets and statins in addition to other medications to control risk factors of cardiovascular diseaseModified Rankin Score of 3 or lessPossession of a personal cell phone that the patient has access to at all times. In the case of patients who do not own, or are unable to use, mobile phones, they must have a caregiver available at all times who possesses a cell phoneAbility to receive, comprehend and reply to an SMS in English or Urdu or Roman Urdu. In the case of patients who themselves are unable to receive, comprehend or reply to an SMS, they must have caregivers available at all times who could perform the above-mentioned tasks

In addition all participants are required to provide a written, informed consent prior to enrollment.

#### Exclusion criteria

Intention to travel within 3 months of recruitmentHistory of current malignancy (diagnosed in the last 5 years and receiving treatment)Planned procedure (in the study time period of 3 months) which necessitates rapid medication changes

### Interventions

#### Intervention group

##### Talking Prescription (*Bolta Parcha*)

At enrollment, patients will be allotted unique identities (IDs). Patients in the intervention group will be given access to an IVR which is specific to each patient in terms of the medicines prescribed to that particular patient. (Fig. 2 – Interactive Voice Recording Menu) The physician’s prescription is transferred and scanned and sent to the central program to customize the IVR output for that particular participant. The intervention primarily focuses on two sets of medications (i.e., anti-platelets and statins) used in the treatment of patients with stroke and with CAD. These two medication groups were chosen as they have been shown to improve cardiovascular outcomes in patients with stroke as well as those with CAD.

**Fig. 2 Fig2:**
[figure not shown]
Interactive Voice Recording Menu. Interactive Voice Recording Work Flow (IVR) –the participant is able to “listen to” his medications and how they work, their side effects and important interactions. All participants hear a mandatory recording that details essential information in addition to detailed descriptions. There is no cost to this recording and they may listen to it as many times as they wish for clarity

Patients in the intervention arm will be given a phone number, which they can call on at any time of day or night, where a voice recording will inform the patient that the call is free of charge and they will now receive a call back from AKUH. The patient will then receive a call within a minute from AKUH where an IVR is being played. A mandatory message is played explaining the important instructions pertaining to all medicines. The recording then lists medicines the patient has been prescribed serially and asks patients to choose to receive information about either one medicine or all the medicines in their prescription. If, for example, the patient chooses one medicine, the recording then lists the options available which the patient can choose from (dose, frequency, how and when to take the medicine, drug-drug and drug-food interactions, side effects) and press the assigned digit. The patient can listen to each subcategory serially, or targeted information as desired, once or multiple times. This service is available free-of-cost 24 hours a day, 7 days a week.

This modality stresses the relevant pharmacodynamics and pharmacokinetics explaining all the relevant information to the patient in an effort to maximize the effectiveness of this service. It focuses on educating the patient on how and when to take the prescribed medication and about the necessary storage and usage instructions. It strives to impart detailed information regarding the prescribed anti-platelets and statins to each patient so that medication knowledge, adherence and proper usage are highlighted. It also addresses the common myths that surround medications in health literacy-challenged areas – e.g., the myth that you can feel your chronic disease, and therefore, if you feel better, you can stop taking your medications.

##### Short Text Message Service (SMS)

In addition to the IVR service described above, the participant in the intervention arm will also receive an automated SMS which is highly personalized, tailored to the medication prescription of that particular participant, with emphasis on anti-platelets and statins. Daily automated medication reminder SMS will be sent to all the participants to remind them to take their medicines. Using SMS, the participants in the intervention arm will be asked if they have taken their anti-platelet/statin medication for that day, and if not, then they will be urged to take the medication then.

Furthermore, a SMS will be sent once weekly to each patient in the intervention group which will reinforce the importance of medication adherence, lifestyle modifications and cardiovascular risk factors. These aim to boost medication adherence and health literacy. The SMS are phrased using the behavior change intervention taxonomy devised by Michie et al. [6].

Using the standardized definitions as presented in the taxonomy allows for easy reproducibility and generalized applicability for future work related to this intervention. The specific content of the SMS is derived from the Social Cognitive Theory and Health Belief Model of behavior change in health care [11, 12]. Templates used include “Pakistanis are at high risk of stroke and heart attack. Please reduce your risk by taking your medicines on time” and “Exercise is good for your health. Try to perform regular exercise.” The purpose of adapting this model for designing SMS is to make them effective in communicating to the participants the consequences of their behavior on health.

Please note that both IVR and SMS will be available in English, Roman Urdu or Urdu based on patient preference. (Additional file 1 – SMS messages).

A hosted SMS gateway provided by our trial technical support (eOcean) is used to send the SMS using web services once upon uploading the medicine prescription onto the application server and daily and weekly SMS requested to the same server according to the participant’s prescription and profile [13].

##### Pill count

On a select sub-set of the intervention group (approximately 20 %) medication adherence will be objectively monitored by doing a pill count. Selected patients are provided with two weekly pill organizers each and their anti-platelets and statins are filled in these organizers for 2 weeks. The patient is then asked to return every 2 weeks for a pill count to objectively assess medication adherence as a direct measure of the intervention being provided to these patients via SMS and Talking Prescription. These patients are required to visit the facility for a pill count every 2 weeks until the cessation of the study (i.e., 3 months).

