The major limitation of this study is the choice of measure of primary outcome, i.e., self-report of medication adherence on the Morisky Medication Adherence Questionnaire [37, 38]. Although this tool has been validated in Urdu in the implementation country, using assessment tools such as biochemical markers or electronic pill boxes may potentially provide more accurate results. This however is not possible because of the complexity of a vascular patient’s prescription; this may include drugs for multiple risk factors and multiple drugs at the same time. Simply opening an electronic pill box registers a dose as administered even if the patient takes only two medicines out of the four he is prescribed for that time, thus an electronic pill box could not capture the data of a complicated regimen. Running biochemical tests for each of these medications would be costly and impractical in a resource- constrained environment and would require repeat hospital visits [39–42]. In any arm, if the design required patients to make repeat visits during intervention and to interact with the caregiver then the act of repeated interaction may then be more responsible for adherence than the IT-based intervention itself. However, we do intend to perform a limited pill count to add robustness and triangulation data to our measures. Another limitation of our study is that we are unable to blind participants to the educational intervention, so those on the intervention arm are receiving SMS and are thus aware that they are on a program to increase literacy and medication compliance. A possible design to account for participant effect due to the lack of blinding could be giving two versions within the intervention where general information may be imparted in one arm and more detailed specific intervention could be imparted to participants in the second intervention arm as compared to the control. At this pilot stage we were unable to plan for two versions in this intervention arm since we were concerned about how this technology would be received and used in this early study.

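### The protocol article places the pill-count sub-set in both arms in one section and in the intervention arm in another; run the second way, it adds an adherence aid to one arm of the primary comparison

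*Protocol article*

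**What the plan says.** The Design overview (text after Fig. 1) states: "In a sub-set of patients (20 % of patients in each group), pill count will be performed". Its stated purpose is the correlation between self-reported MMAS and the count. It mentions neither organisers nor extra visits.

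The Pill count section, placed under the Intervention group heading, opens with the words "On a select sub-set of the intervention group", puts that sub-set at about 20%, and has its adherence monitored by pill count. It adds: "Selected patients are provided with two weekly pill organizers each and their anti-platelets and statins are filled in these organizers for 2 weeks", and: "These patients are required to visit the facility for a pill count every 2 weeks until the cessation of the study". It presents the count as measuring directly what SMS and the Talking Prescription deliver to these patients.

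The Control group section lists clinic visits, counselling, reading material, a helpline and appointment reminders. It mentions no organisers, pill counts or extra visits. The Study timeline and Data collection methods sections refer to a selected sub-set or sample without naming an arm. The Study timeline says that everyone outside the sub-set has only the 3-month study visit. Statistical methods analyses all patients in the arm to which they were randomised.

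**The concern.** Staff who follow the Design overview and staff who follow the Pill count section would run different trials. In the second, about one fifth of the intervention arm receives filled organisers and fortnightly visits, and no control patient does.

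The Discussion gives the reason why this matters. It explains that, had the design required repeat visits, "the act of repeated interaction may then be more responsible for adherence than the IT-based intervention itself". The same reasoning applies to the sub-set. Any benefit from organisers and visits would enter the primary MMAS difference and be credited to IVR and SMS. The Control group section's assurance that the design prevents overestimation of the effect would then not hold.

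There is a second consequence. Data collection methods has the research officer, described as blinded to allocation, perform the pill counts. If only intervention patients are counted, an officer who knows this also knows the allocation of every patient counted.

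**Working it through.** **Which arms.** The two statements and the sections that might settle them:

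| Section | Arm(s) | What is given |
|---|---|---|
| Design overview | each arm, 20% | pill count |
| Pill count (under Intervention group) | intervention arm, about 20% | pill count, filled organisers, visits every 2 weeks |
| Control group | controls | none of these mentioned |
| Study timeline; Data collection methods | not named | pill count every 2 weeks |

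Nothing resolves the first two rows.

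**Inputs.** From Sample size: 1-point MMAS difference, power 90%, significance level 5%, 86 per arm, 100 per arm after 15% attrition. From Statistical methods: two-sided testing. From Pill count: share 0.20. The documents give no SD and no effect of organisers plus visits; call that effect d.

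**The plan's own figure.** n per arm = 2 × SD² × (1.960 + 1.282)² / 1². Setting n = 86 gives SD = √(86 / (2 × 10.51)) = 2.02. With an assumed SD of 2.0 the normal formula gives 84.1, rounded up to 85, and the t-based calculation gives 85.03, rounded up to 86. So 86 fits an SD of about 2.0, which is an assumption here. For attrition, 86 / 0.85 = 101.2, close to the stated 100. The point does not depend on the sample size.

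**Shift if the sub-set is in the intervention arm only.** Shift in the mean difference = 0.20 × d − 0 × d = 0.2d, towards the intervention if d is positive.

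**Illustrative consequence for the test.** SE = 2.0 × √(2/86) = 0.305. If IVR and SMS had no effect, the probability of a significant result is Φ(0.2d/SE − 1.96) + Φ(−0.2d/SE − 1.96).

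| Assumed d (points) | Shift (points) | Share of 1-point target | Rejection probability |
|---|---|---|---|
| 0 | 0 | 0% | 5% |
| 0.5 | 0.10 | 10% | about 6% |
| 1 | 0.20 | 20% | about 10% |
| 2 | 0.40 | 40% | about 26% |

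**Shift if the sub-set is 20% of each arm.** Let d_I and d_C be the aid's effect in intervention and control patients. The shift is 0.2 × (d_I − d_C). It is zero if the two are equal. If the aid adds less for patients who already get daily SMS, for example d_I = 0.5 and d_C = 1, the shift is 0.2 × (−0.5) = −0.10, against the intervention.

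**Cost in power of excluding 20% of each arm.** 0.8 × 86 = 68.8, about 69 per arm. SE = 2.0 × √(2/69) = 0.341. Power for 1 point = Φ(1/0.341 − 1.96) = Φ(0.98), about 84%. That is adequate for a sensitivity analysis.

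**The case against.** The strongest reply is that the Pill count section never says controls are left out. It sits under the intervention heading and may simply describe that arm's share of a sub-set drawn from both; the Design overview is the only place that speaks of both arms. This stands in part: a one-arm design is not established. But the section ties the count to SMS and the Talking Prescription, which controls do not receive, and the Control group section has no counterpart. The text leans towards one arm and leaves the matter open.

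Second, the size is assumed. A d of 1 equals the whole target effect and a d of 2 is twice that, on top of IVR and daily SMS and on a scale that ends at 8. This stands: the shift and rejection probabilities are illustrations, and d may be near zero.

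Third, the authors weighed repeat contact in the Discussion and chose only a limited pill count. That limits the exposure to about a fifth of patients, but does not make it equal between arms.

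A reader might also infer that sub-set patients were hand-picked. The article says only that they are selected, and how they are drawn is detail an article may leave to the full protocol. Nor does the Design overview promise organisers and visits to controls; it promises a pill count.

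**Conclusion.** The contradiction is real and no section of the article resolves it. If the trial is run as the Pill count section reads, the primary MMAS difference shifts by 0.2d: 0.10 to 0.40 points for an assumed d of 0.5 to 2, and zero if the aid has no effect. The direction, if d is positive, favours the intervention. In that version the assessor's blinding would also be compromised for about 20 patients.

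A reader might go further and conclude that the primary result is biased, or that the type I error is 10% or more. The documents do not support that. They do not show which version is run, they give neither d nor the SD, and the shift cannot exceed one fifth of d. The conclusion is conditional on the one-arm reading, and the rejection probabilities also rest on an SD of about 2.0 inferred from the stated sample size.

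**What to change.** Reconcile the Design overview, Pill count, Control group, Study timeline and Data collection methods sections so that all state the same thing: a randomly chosen 20% of each arm, with identical organisers, visits and counting procedures. The Clinical Trials Unit can do this within the existing randomisation. Each block of 10 holds 5 envelopes per arm; flagging one per arm in each block gives 1/5 = 20%, and over 200/10 = 20 blocks gives 20 patients per arm. Being counted then says nothing about allocation.

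Pre-specify a sensitivity analysis of the primary outcome that excludes the pill-count patients. It is needed because equal sub-sets cancel the shift only if the aid works about equally in both arms. Random selection is what keeps the remaining patients a fair comparison.

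Cost: a protocol amendment with ethics committee approval and a registry update, flagged envelopes, and one extra analysis. If the Design overview version was already planned, no further patients are counted. If only the intervention-arm version was budgeted, about 20 controls need organisers and roughly six fortnightly visits each (about 20 × 6 = 120 visits, with travel reimbursed), and those controls no longer receive usual care alone.

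The article gives the trial as ongoing, so flagging can apply only to patients not yet randomised. For those already counted, the report should state which arm they came from and how they were chosen.
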